## Methods

### Participants

For this study, we will recruit approximately 655 participants from each of the selected University of Florida (UF) outpatient specialty clinics. This sample size was specifically chosen as a result of statistical analysis that suggests this study population would indicate a powered study. There is no control group, as this was an observational study. Due to the nature of our enrollment process, which does not require a follow-up visit, we expect a <1% attrition rate, reaching a desired ~655 samples per site based on our power analysis. Study participants will be between the ages of 18 and 99 years.

Eligible participants are any patient visiting the UF Nephrology Clinic, UF Sleep Clinic, UF Neurology Clinic, UF Ophthalmology Clinic, UF Urology Clinic, and UF Pre-Surgical Center. Patients with a history of AFib will not be excluded from the study, as they provide valuable data on potential risk factors and may be prone to AFib recurrence. Participants were only excluded if they were younger than 18 years of age, a leg or hand amputee, a paralyzed person, unable to consent, or unable to read and comprehend English.

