### Statistical Analysis

The information collected from the study is categorical data: accurate versus inaccurate. We will be performing an interrater reliability test using Cohen κ coefficient for each of the individuals making a preliminary diagnosis. This will give us a level of agreement. All tests will be 2-sided, and *P* values <.001 will be considered statistically significant.

The number of participants required to achieve statistical significance for this study was calculated to be 655 after completing a power analysis for a 2×2 contingency table design. The probability of a positive diagnosis was .84 and .82 for KardiaMobile and standard ECG, respectively, after applying published literature findings on the efficacy of both methods. Applying Cohen κ statistic, we are looking at the agreement between the 2 metrics to see if KardiaMobile is an effective prescreen. Additional statistical methods include direct comparison, noninferiority, superiority, qualitative comparison, sensitivity, and specificity.

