## Results

As of March 1, 2024, a total of 2339 participants have been enrolled. Of the 6 UF Health specialty clinics, 335 were from the UF Health Nephrology Clinic, 466 from the UF Health Sleep Clinic, 597 from the UF Health Ophthalmology Clinic, 526 from the UF Health Urology Clinic, 231 from the UF Health Neurology Clinic, and 184 from the UF Health Pre-Surgical Clinic. The participants’ ages ranged from 18 to 99 years, with an average age of 61 (SD 10.25) years. The average weight of all participants is 194 (SD 14.26) lbs. The race distribution was reported to be 266 (11.42%) African American, 51 (2.18%) Asian, 124 (5.30%) Latino, 1818 (77.73%) White, and 80 (2.61%) others.

The KardiaMobile rhythm strip reported 381 abnormal readings, which are pending analysis from a cardiologist. A total of 78 readings were labeled as possible AFib, 159 readings were labeled unclassified, and 49 were unreadable. Additionally, 1573 (67.25%) of participants report not regularly seeing a cardiologist.

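### 655 is the requirement for the study in one section and for each of six clinics in another, and under 1% attrition does not yield 655 paired ECG results

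*Protocol article*

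**What the plan says.** The article gives the sample size twice.

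- Statistical Analysis: "The number of participants required to achieve statistical significance for this study was calculated to be 655". The design behind this figure is a 2×2 table, and the stated inputs are: "The probability of a positive diagnosis was .84 and .82 for KardiaMobile and standard ECG, respectively".
- Participants: "we will recruit approximately 655 participants from each of the selected University of Florida (UF) outpatient specialty clinics", followed by "we expect a <1% attrition rate, reaching a desired ~655 samples per site based on our power analysis". The reason given for low attrition is an enrolment process "which does not require a follow-up visit".

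Three other places determine what the number has to deliver. Detection Accuracy, under Primary Measures, compares the device result with the standard 12-lead ECG, and it lists unreadable and unclassified among the possible device results. Procedure has the treating physician informed of an irregular device finding and brings in a 12-lead ECG where the participant has no history of arrhythmia. Results reports 2,339 participants and 381 abnormal readings at the March 2024 cut.

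**The concern.** One power analysis cannot yield both 655 for the study and 655 for each of six clinics unless a clinic-level question was being powered. None appears in Specific Aims, Primary Measures or Statistical Analysis. The reader therefore cannot tell what the sized analysis is, or whether a result from a single clinic is meant to carry confirmatory weight.

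The attrition sentence then treats enrolment as if it delivered the analysed sample. For an agreement or accuracy analysis against a 12-lead ECG, the unit is a participant with both results. Someone who is enrolled, recorded once and never given the reference ECG counts as no loss under the article's definition but contributes nothing to the paired table. The stated sample size would then overstate the precision of the accuracy result.

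**Working it through.** **Inputs.** 655 (Statistical Analysis; Participants); six clinics and under 1% attrition (Participants); rates 0.84 and 0.82 (Statistical Analysis); 2,339 enrolled and 381 abnormal readings (Results); route to the 12-lead ECG (Procedure).

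**1. Can 655 be reproduced, and does that show which level it belongs to?** The two-proportion formula is n per group = [z(α/2)·√(2·p̄·q̄) + z(β)·√(p₁q₁ + p₂q₂)]² / (p₁ − p₂)². Statistical Analysis says "All tests will be 2-sided". Power is not stated, nor is the α used in the power analysis, so I assume 0.05 and 80%:

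- p̄ = 0.83, so √(2 × 0.83 × 0.17) = 0.5312
- √(0.84 × 0.16 + 0.82 × 0.18) = 0.5310
- n = (1.960 × 0.5312 + 0.8416 × 0.5310)² / 0.02² = 5,537 per group

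This is not 655. Other settings come close:

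- paired McNemar test, two-sided 0.05, 80% power, total discordance about 3.35%: 655
- non-inferiority margin of 0.06 with both rates 0.82, one-sided 0.025, 80% power: 644
- kappa of 0.7 against 0.8, two-sided 0.05, 80% power: 660

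Each needs an input that the article does not state. The calculation therefore cannot settle whether 655 is a study or a clinic number, and the wording has to.

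**2. The two totals.** Study reading: 655. Clinic reading: 6 × 655 = 3,930. Current enrolment is 2,339/655 = 3.6 times the first and 2,339/3,930 = 59.5% of the second. On one reading recruitment passed its goal long ago; on the other it is still under way.

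**3. What the attrition figure covers.** A 1% loss would change 655 to 655/(1 − 0.01) = 662, which is negligible. The stated reason concerns return visits only and says nothing about who receives the reference ECG.

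**4. How many pairs the described pathway can give.** The upper bound is the share with an abnormal reading: 381/2,339 = 0.1629, assuming one reading per participant.

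| Enrolled | Maximum pairs (enrolled × 0.1629) |
|---|---|
| 655 | 107 |
| 2,339 | 381 |
| 3,930 | 640 |

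This is a ceiling. Participants with a history of arrhythmia come out of it, and so does anyone for whom no 12-lead ECG is done. Even at the ceiling, 655 pairs would need 655/0.1629, or about 4,021 enrolled.

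**5. Effect on precision.** The width of a confidence interval for a proportion varies as 1/√n. If 655 was meant as pairs within a clinic, 107 pairs give intervals √(655/107) = 2.5 times as wide. Pooled over 3,930 enrolled, the ceiling of 640 is close to 655, with a ratio of √(655/640) = 1.01. The shortfall therefore bites hardest on the per-clinic claim.

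**The case against.** The strongest reply is that Statistical Analysis never says the 655 is pooled over clinics. It could be the requirement for one 2×2 table, repeated in each clinic, with the clinic-level reasoning left to a fuller document. That stands as a possibility, and it is why the fix is conditional. It does not remove the conflict, because both statements are explicit, name the same power analysis and give totals that differ sixfold.

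A second reply is that reference results may come from elsewhere. Procedure also mentions comparison with the medical record, and 12-lead ECGs done for other reasons would add pairs. This also stands in part. But Detection Accuracy names the 12-lead ECG as the comparator, and the article gives no number for ECGs already on record.

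Three stronger readings are tempting and are not supported:

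- **That the per-site target has failed because no clinic had reached 655.** Results lists, for example, "231 from the UF Health Neurology Clinic, and 184 from the UF Health Pre-Surgical Clinic". But these are counts at a data cut while collection continued, and the target is written in the future tense. They describe recruitment progress and do not show a faulty target.
- **That unclassified and unreadable readings (159 + 49 = 208 of 2,339, or 8.9%) contradict under 1% attrition.** Detection Accuracy lists both as device results, and the Discussion keeps them among the abnormal findings as representative of the device. By the plan's own rules they are outcomes and not losses, and subtracting them would tend to flatter accuracy.
- **That the Discussion concludes as though the powered size had been met.** It mentions neither power nor 655, and it calls its findings preliminary.

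**Conclusion.** The point holds on two grounds. First, the sample-size basis contradicts itself: 655 for the study against 3,930 across six clinics, both credited to one calculation, with no stated clinic-level question. Second, the under-1% figure does not secure 655 paired results. The pathway described gives at most 16.3% of those enrolled, about 107 per 655 and about 640 at 3,930.

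The pair counts assume one reading per participant, an abnormal rate that stays at its interim level, every abnormal reading counting as irregular and leading to a 12-lead ECG, and no reference ECGs from other sources. The first three make the figures generous. Relaxing the last would raise them by an amount the article does not allow one to estimate. The contradiction depends on none of these assumptions. This should be corrected before accuracy results are reported; it does not invalidate the data collected.

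**What to change.** - Reconcile Participants with Statistical Analysis by stating whether 655 is the study or the per-clinic requirement, and for which analysis.
- Unless a clinic-level hypothesis exists, make the pooled analysis, stratified by clinic, the one that is sized. Delete the per-site powering claim and report clinic results as descriptive with confidence intervals. If such a hypothesis does exist, state it and show the calculation that gives 655 for it.
- Replace the under-1% attrition statement with the expected number of participants who have both a device result and a reference ECG, and restate precision on that number.
- Keep unclassified and unreadable readings in the denominator as outcome categories.

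The cost is wording and recalculated figures, with no additional patients. The downside is that per-clinic powering claims are given up and the stated precision becomes less favourable.

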To diagnose AFib, an electrocardiogram (ECG) reading must show irregular R-wave intervals without distinct P waves [10,11]. Standard 12-lead ECGs are costly and time-consuming devices that are used to detect AFib [12,13]. The development of new devices like the single-lead portable, phone-based KardiaMobile device (AliveCor) may be an efficient and cost-effective alternative to the standard 12-lead ECGs that can potentially offer feasible mass screenings for AFib [14,15]. The standardization of mass screenings for AFib in primary and outpatient clinics can thus help improve the implementation of prevention strategies for cardiovascular diseases [16]. Costs, availability, and time required to use ECG machines are prohibitive factors for conducting regular ECGs [17,18].

Timely identification of AFib plays a crucial role in reducing mortality rates, allowing for an opportunity to cardiovert the patient, start the patient on anticoagulant therapy, and apply catheter ablation techniques [19,20]. AFib is often asymptomatic; thus, many cases may go undiagnosed without any screening mechanisms in place. A retrospective modeling study published in 2018 discovered that 1.3% of older patients and 0.9% of working-age adults went undiagnosed for AFib [8,21]. To decrease this gap of undiagnosed cases and improve the health care of patients, it is primordial to implement feasible screening and prevention strategies. A 2018 study published in the *Journal of Arrhythmias* reviewed portable out-of-hospital ECG devices [22,23]. Of the devices that they reviewed, AliveCor’s KardiaMobile device was determined to be accurate in measuring QTC wave intervals on ECG and was found to have a sensitivity of 98.5% and a specificity of 91.4% in pharmacy patients older than 65 years [24,25].

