### Specific Aims

The aim of this study is to demonstrate the feasibility of performing Kardia-enabled ECG recordings routinely in outpatient settings in high-risk populations and its potential use in uncovering previously undiagnosed cases of AFib. Specific aim 1 is to determine the feasibility and accuracy of performing routine cardiac rhythm sampling in patients deemed at high risk for AFib. Specific aim 2 is to determine whether routine rhythm sampling in outpatient clinics with high-risk patients can be used cost-effectively in an outpatient clinic without increasing the time it takes for the patient to be seen by a physician.

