### Recruitment

Participants will be recruited for the study under the title “Mobile ECGs in Detection of Subclinical AFib in High-Risk Outpatient Populations.” Study participants will be approached by a research assistant trained in informed consent and will be asked if they are interested in learning more information about this study. If they are interested, the research assistant will discuss the goals of the study as well as potential risks. If the participant agrees to participate in the study, the research assistant will provide them with informed consent and a questionnaire for them to fill out that aims to reveal any risk factors for cardiovascular disease.

Participants enrolled in the study will receive a standardized data collection code in the format of “NEP,” the number of weeks, and the number of participants enrolled that week. For example, NEP0101 will indicate the first participant enrolled during the first week of the study. This will allow for participant data to remain confidential during the data analysis portion of the study. A master sheet of the collection codes and the associated participant study data will be stored on an institutional review board (IRB)–approved, secure study Dropbox.

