The number of patients who were screened as having AFib and had an abnormal ECG reading will be compared by using the participant’s medical record on Epic Systems. The number of positive screens versus negative screens will also be compared to assess the sensitivity and specificity of testing in the given population.

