##### Heart Health

The final section of the questionnaire focuses on the patients’ cardiac health and their experience with a cardiologist. The questions and response choices are as follows:

“Have you personally ever been diagnosed with any of the following cardiac conditions?”Atrial fibrillation, cardiomyopathy, heart stents, congestive heart failure, heart attack, coronary artery disease, hypertension, stroke, and pacemaker or defibrillator“Are you currently being seen by a cardiologist?”Yes: When is your next scheduled appointment? (eg, 03/2030)No: When is your next scheduled appointment with a primary care physician?

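### Known AFib patients are pooled with everyone else, so the accuracy stated for previously undiagnosed AFib is not supported by the sample described

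*Protocol article*

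**What the plan says.** The Specific Aims pair feasibility with "its potential use in uncovering previously undiagnosed cases of AFib". The study is presented to patients as "Mobile ECGs in Detection of Subclinical AFib in High-Risk Outpatient Populations".

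The Participants section then states: "Patients with a history of AFib will not be excluded from the study". The reason given is that such patients are kept "as they provide valuable data on potential risk factors and may be prone to AFib recurrence".

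Prior AFib is recorded. The Heart Health questionnaire asks "Have you personally ever been diagnosed with any of the following cardiac conditions", and atrial fibrillation is the first response choice.

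For the analysis, the Procedure section says: "The number of patients who were screened as having AFib and had an abnormal ECG reading will be compared by using the participant’s medical record". It adds that sensitivity and specificity will be assessed in the population tested, without restriction by history. The Statistical Analysis section lists sensitivity and specificity again, also without a subset. Detection Accuracy, a primary measure, names the standard 12-lead ECG as the comparator.

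The Results give 78 possible-AFib readings and 381 abnormal readings for 2,339 enrolled participants and do not say how many had AFib before. The Discussion describes 95% sensitivity and 97% specificity as accuracy for AFib not diagnosed before, and its closing paragraph draws public-health implications from detecting such cases.

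**The concern.** A claim about new AFib needs a population in which AFib, if present, would be new. Here the people analysed include some whose AFib is already in the record, and nothing described takes them out before the claim is made.

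Two statements are affected. The first is the accuracy label in the Discussion: a sensitivity estimated over known and new cases together is not the sensitivity for new cases. The second is any detection rate taken from the pooled count: a known patient who happens to be in AFib during the strip adds to the 78 but is not a discovery.

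The reference also matters. If rhythm on a 12-lead is the truth, a known patient is simply another test of the device. If the medical record is used as the truth, a known paroxysmal patient in sinus rhythm can be scored as a missed case, and a known patient in AFib as a detected one. Neither says anything about new detection, and the two push sensitivity in opposite directions. At stake is whether the reported figures can carry the study's public-health conclusion.

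**Working it through.** **Figures in the document.** The six clinic counts reproduce the denominator: 335 + 466 + 597 + 526 + 231 + 184 = 2,339. The pooled flag rate is 78/2,339 = 3.33%. The 95% and 97% cannot be reproduced, because the counts behind them are not given.

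**What would be needed.** Let K be the number with prior AFib and x the number of them among the 78. The flag rate in people without a history is (78 − x)/(2,339 − K). The pooled rate exceeds it whenever known patients are flagged more often than the rest. Neither K nor x is reported, so the quantity cannot be computed.

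**Illustration of scale.** Assumptions:
- K = 2,339 × k, with k = 2.3% or 5.9%. These are the general prevalences in the Introduction (over 40 and over 65 years), used here as stand-ins for known AFib in these clinics.
- A share f of known patients is in AFib during the 30-second strip. The document gives no value; 0.25, 0.50 and 0.75 are assumed.
- The device flags 95% of those, so x = 2,339 × k × f × 0.95.

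| k | f | x | (78 − x)/(2,339 − K) | pooled ÷ this |
|---|---|---|---|---|
| 2.3% | 0.25 | 12.8 | 2.85% | 1.17 |
| 2.3% | 0.50 | 25.6 | 2.30% | 1.45 |
| 2.3% | 0.75 | 38.3 | 1.74% | 1.92 |
| 5.9% | 0.25 | 32.8 | 2.05% | 1.62 |
| 5.9% | 0.50 | 65.6 | 0.57% | 5.9 |
| 5.9% | 0.75 | 98.3 | not possible, x exceeds 78 | – |

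For the first row: 2,339 × 0.023 = 53.8; × 0.25 × 0.95 = 12.8; (78 − 12.8)/(2,339 − 53.8) = 65.2/2,285.2 = 2.85%; 3.33/2.85 = 1.17.

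These are flag rates. The 78 include false positives, so even the no-history column is not a rate of confirmed new AFib.

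**A second indication.** The Introduction gives 16% to 21% AFib in chronic kidney disease without dialysis. If that applied to all 335 nephrology participants, the clinic alone would hold 0.16 × 335 = 54 to 0.21 × 335 = 70 people with AFib, diagnosed or not. Against 78 flags in total, known cases could be a material part.

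**Reference by history.** The Procedure section describes the 12-lead decision for participants without an arrhythmia history and is silent on the others. The flow diagram has a cardiologist read the strips, with a confirmatory 12-lead where indicated and no mention of history. Detection Accuracy uses the 12-lead; the Procedure comparison uses the medical record. These passages do not settle which reference applies to participants with a history.

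**The case against.** The strongest reply is that enrolling known AFib is deliberate and suits the listed primary measures. For agreement between device rhythm and 12-lead rhythm, known patients are legitimate and supply scarce positives; for feasibility, history is irrelevant. Prior AFib is asked of every participant, arrhythmia history is used in the procedure, the Abstract speaks of newly diagnosed AFib, and the record is consulted. Separation is therefore possible, and a fuller plan could specify it. All of that stands. It does not rescue the Discussion, which attaches a result to a population that no described step isolates. That is a statement made, not a detail left out.

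Three stronger readings are tempting and not supported:

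- A reader might infer that screening yield **is** inflated. No yield endpoint is defined, the 78 are labelled only possible AFib, and the abnormal readings await a cardiologist. They are not called new cases.
- A reader might set 3.3% against the Introduction's figures, "1.3% of older patients and 0.9% of working-age adults went undiagnosed for AFib", and take the gap as the bias. That compares device flags with a rate of true disease. At 97% specificity, false positives alone would be 0.03 × 2,201 = 66 (with 5.9% AFib) to 0.03 × 2,339 = 70, which could account for nearly all of the gap with no known case among the 78. Subtracting the undiagnosed rates from the prevalences to obtain a known share fails too: the rates come from different sources and age groups, and the result would describe history in the sample, not among the 78.
- A reader might infer that known patients have no reference test. The Procedure section is silent about them; it does not deny them a 12-lead.

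**Conclusion.** The mismatch is real and visible in the text. The aim, the recruitment title and the conclusion concern undiagnosed or subclinical AFib; the sample includes known AFib; and the planned accuracy analysis and reported counts are pooled. The 95% and 97% cannot stand as accuracy for undiagnosed AFib on the sample described.

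The pooled 3.3% overstates new-AFib detection only if it is read as such and if known patients are flagged more often than others, which is likely but not shown. The illustrative ratio of 1.17 to 5.9 rests on general-population prevalences and assumed shares in AFib during the strip, so it shows that the effect could be small or large and is not an estimate. For sensitivity and specificity, even the direction of any bias is unknown until the reference is fixed. Feasibility and device-versus-12-lead rhythm agreement are not undermined by including known cases.

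**What to change.** - Base any yield, positive predictive value or accuracy claim about new or undiagnosed AFib on participants with no AFib on the questionnaire **and** no AFib diagnosis in the medical record before the screening date.
- Report participants with known AFib separately, and give their number overall, among the 381 abnormal readings and among the 78.
- Keep all participants for feasibility and for device-versus-12-lead agreement, with rhythm at the time of recording as the target.
- Either relabel the 95% and 97% as whole-sample accuracy or recompute them in the no-history subset, with the counts.
- Reconcile the Procedure and Detection Accuracy sections on which reference applies to participants with an arrhythmia history.

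No new enrolment or questionnaire item is needed; the work is a filter on collected answers plus a dated record lookup. The price is fewer positives, wider intervals and possibly a lower stated detection rate.
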